### Randomisation and blinding

Participants will be randomised 1:1 to receive either ambroxol or placebo. Randomisation will be implemented using a minimisation algorithm incorporating a random element to achieve overall balance between the randomised groups by research site, Movement Disorders Society–Unified Parkinson’s Disease Rating Scale (MDS-UPDRS) part III, *GBA1* mutation status, age, time since PD diagnosis, and levodopa equivalent dose.

The treatment allocation will be concealed from all trial personnel, including investigators, pharmacy staff, research teams at sites, participants, and the analysing trial statistician prior to assignment and during the trial, until the final participant has completed the double blind phase, and the database is locked.

Before database lock, the only data summarised by treatment allocation will be within reports to the Independent Data Monitoring Committee (IDMC), which will not be distributed outside of this committee. The unblinded statistician will be responsible for preparing these reports and will be the only person outside the IDMC who will have access to these reports. Unblinded statisticians will be excluded from any discussion on the implementation or planning of the trial.

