**Fig. 1 Fig1:**
[figure not shown]
AsPRO-PD trial diagram

Participants who opted to participate in the CSF sub-study will provide a CSF sample at visit 1 and at visit 6 (104 weeks).

The primary outcome is the sum score of MDS-UPDRS parts I-III (part III measured in OFF medication state) assessed at 104 weeks after randomisation. OFF medication state is defined as not having taken any PD medication for 8 h in the case of short acting agents or ≥ 24 h in the case of longer acting agents (e.g. once-daily dopamine agonists). Irreversible monoamine oxidase type B inhibitors (MAOBIs) will only be stopped the morning of the assessment and then taken after the OFF examination. It is accepted that the long half-life of MAOBIs make alternative arrangements impractical.

Different personnel will assess primary outcome measures from those documenting adverse event data to minimise risk of rater bias/inadvertent unblinding. Secondary outcomes will be assessed non-hierarchically and include the rate of change of MDS-UPDRS composite scores of parts I–III and of part III from baseline to 104 weeks, and the following outcome measures at 104 weeks: the individual scores of MDS-UPDRS parts I, II, III and IV, MoCA, Trial Making Test parts A and B [25], Hooper Visual Organization Test (VOT) [26], Parkinson’s disease 39 item Quality of Life questionnaire (PDQ-39) [27], Patient Global Impression (PGI) Severity and Change [28], EuroQol Eq-5D 5-Level Health Related Quality of Life Questionnaire [29], Non-Motor Symptoms Scale (NMSS) [30], Parkinson’s Disease Comprehensive Response (PD CORE) [31], Dresden Falls Questionnaire (DREFAQ) [32], Clinical Global Impression (CGI) [28], and change in levodopa equivalent dose. Safety and tolerability measures and time to initiation of rescue medication will also be included in secondary outcomes. Mechanistic outcomes include differences in GCase activity, GCase protein levels and alpha synuclein protein levels in blood and CSF and additionally glucosylceramide, neurofilament light chain (NFL), TAU protein and lipid profile in CSF. Further exploratory outcomes are comparison of change in MDS-UPDRS at 104 weeks from baseline by subgroup *GBA1* mutation status, analysis of *GBA1* positive and negative carrier data against placebo, change in MDS-UPDRS at 130 weeks from baseline, change in the gut microbiome composition at 104 weeks from baseline, and change in UPSIT at 104 weeks from baseline.

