### Statistical considerations

The sample size is calculated based on estimating the average difference in MDS-UPDRS at Week 104 conditional on the baseline scores, at the 2.5% significance level in a one-sided test of superiority of ambroxol over placebo. A standard deviation of 14, a correlation of 0.7 between the outcome and baseline and 20% attrition percentage was assumed based on previous studies and data from the Exenatide-PD trial [33]. The proposed sample size has 90% power to detect the minimum important difference of 4 in MDS-UPDRS I–III at the 2.5% (one-sided) significance level.

Summary measures will be presented as means and standard deviations for normally distributed variables, medians and interquartile ranges for non-normally distributed variables, and frequencies and percentages for categorical variables.

A multilevel repeated measures linear regression model will be used to estimate the difference (with 95% confidence intervals) in MDS-UPDRS (parts I–III) scores between ambroxol and placebo, following the intention-to-treat principle. The model will include fixed effects for the intervention groups (ambroxol or placebo) and the minimisation factors (i.e. the co-variates) *GBA1* mutation status (wild-type, severe variant carrier, non-severe variant carrier), age, time since diagnosis and the levodopa equivalent dose. Baseline scores will be accounted for using a random intercept term to address clustering of repeated measurements within participants. Additionally, a random effect for site and patient effect will be included to take account of clustering. This model for the primary outcome will be extended using an interaction term to investigate whether the effect of treatment differs according to *GBA1* status, as a pre-specified subgroup analysis.

Changes to participants’ standard Parkinson medication (e.g. levodopa etc.) will be allowed during the trial. A levodopa equivalent dose (LED) will be calculated, and a causal mediation analysis may be carried out as a sensitivity analysis of the primary outcome to assess if differences in LED levels between treatment arms mediate any observed treatment effect on the primary outcome.

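### The primary model names only a participant random intercept and no visit terms: as written it does not estimate the Week 104 difference, and a Week 104 contrast taken from it may carry too small a standard error

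*Protocol article*

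**What the plan says.** All references are to the protocol article.

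- **Endpoint** (Assessment of participants and outcomes): "The primary outcome is the sum score of MDS-UPDRS parts I-III (part III measured in OFF medication state) assessed at 104 weeks after randomisation". Visits in the blinded phase are at baseline and weeks 20, 40, 60, 80 and 104.
- **Sample size** (Statistical considerations): based on the Week 104 difference conditional on baseline, "at the 2.5% significance level in a one-sided test of superiority of ambroxol over placebo". The inputs are: "A standard deviation of 14, a correlation of 0.7 between the outcome and baseline and 20% attrition percentage was assumed". The claim is "90% power to detect the minimum important difference of 4 in MDS-UPDRS I–III", with 330 participants randomised 1:1.
- **Primary model** (Statistical considerations): a multilevel repeated-measures linear regression. The fixed effects named are arm and minimisation factors. Baseline and within-participant dependence are handled together: "Baseline scores will be accounted for using a random intercept term to address clustering of repeated measurements within participants". The next sentence reads: "Additionally, a random effect for site and patient effect will be included to take account of clustering".

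The model description names no visit term, arm-by-visit term, random slope, residual covariance structure or robust standard error. A detailed SAP is promised before database lock and is not shown.

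**The concern.** The endpoint and sample size refer to one visit, conditional on baseline. The model as described does not deliver that quantity.

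1. With no arm-by-visit term, the arm coefficient is an average over visits.
2. A random intercept does not condition on baseline in the sense of the sample-size calculation. It lets participants differ in overall level. The patient effect in the next sentence is, as written, the same participant-level intercept again and cannot be estimated separately.
3. A random intercept with independent residuals means compound symmetry: one variance for all visits and one correlation for every pair. If correlation falls with time, or participants progress at different rates, the variance remaining after baseline adjustment is largest at Week 104. The model would give that visit the pooled, smaller variance.

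Adding only an arm-by-visit term would repair the first point and expose the third. At stake are what the primary result means and whether its one-sided 2.5% level and 95% confidence interval can be trusted.

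**Working it through.** **Inputs from the article:** difference 4, SD 14, baseline-to-Week-104 correlation 0.7, one-sided alpha 0.025, power 90%, attrition 20%, N = 330, 1:1 allocation, visits at weeks 20, 40, 60, 80, 104.

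**Assumed, because not given:** correlations between the other visits, and the SD at each visit. A range is shown.

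**Step 1. The plan's own figure.**
- Residual variance given baseline: 14² × (1 − 0.7²) = 196 × 0.51 = 99.96.
- Per arm: 2 × (1.960 + 1.282)² × 99.96 / 4² = 131.3, so 132.
- Total 264; 264 / 0.8 = 330. This reproduces.
- SE with 132 completers per arm: √(2 × 99.96 / 132) = 1.23. Power: Φ(4 / 1.2307 − 1.96) = 0.9015.

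**Step 2. The model as literally written (arm main effect only).**
- Large-sample comparison of model-based and true SE gives a ratio of 1.00, hence one-sided alpha 0.025, in every covariance scenario tried.
- What it estimates: if the difference grows linearly to 4 points at Week 104 (an assumption), the post-baseline average is 4 × (20 + 40 + 60 + 80 + 104) / (5 × 104) = 2.3 points.
- The averaged contrast also has a smaller SE than the Week 104 contrast, so the point here is the quantity estimated and not mainly power.

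**Step 3. A Week 104 contrast from a random-intercept model, baseline as covariate.** Let v(t) be the variance at visit t given baseline, SD(t)² × (1 − r(t)²), with r(t) the correlation with baseline. With complete data the model uses the mean of v(t) over the five visits in place of v(104), so

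SE ratio = √(mean v(t) / v(104)), and one-sided alpha = 1 − Φ(1.96 × ratio).

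For exponential decay with a share m of the variance due to measurement error, r(t) = (1 − m) × (0.7 / (1 − m))^(t/104). This keeps r(104) = 0.7.

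| Assumed truth | v(t) as % of v(104) | SE ratio | One-sided alpha | 95% CI coverage |
|---|---|---|---|---|
| Decay, m = 0 | 25, 47, 66, 83, 100 | 0.80 | 5.8% | 88% |
| Decay, m = 10% | 52, 65, 77, 88, 100 | 0.875 | 4.3% | 91% |
| Decay, m = 20% | 77, 83, 89, 94, 100 | 0.94 | 3.3% | 93.5% |
| Decay, m = 25% | 89, 91, 94, 97, 100 | 0.97 | 2.9% | 94% |
| m = 30% (constant correlation 0.7) | 100 throughout | 1.00 | 2.5% | 95% |
| Random intercept and slope, SD 14 at both ends, residual variance 50 | 87, 88, 90, 94, 100 | 0.96 | 3.0% | 94% |
| Same, residual variance 30 | 56, 60, 68, 80, 100 | 0.85 | 4.7% | 91% |
| Same, residual variance 20 | 39, 45, 57, 73, 100 | 0.79 | 6.0% | 88% |

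**Step 4. Other SD patterns (random slope, residual variance 30).**
- SD rising from 14 to 17: alpha 5.9% with baseline as covariate and 7.8% with baseline kept among the modelled outcomes.
- SD falling from 14 to 12: 3.8–4.0%.

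These results are asymptotic, ignore the site effect and treat dropout as 0% or 20% completely at random. Dropout changes them little.

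**The case against.** The strongest reply is that the article does not say the random intercept is the only structure. A random intercept can sit alongside a structured residual matrix or robust standard errors. Residual covariance, degrees of freedom and SE method are ordinary SAP content. To obtain inflation one must supply an arm-by-visit term that the article omits while assuming that nothing else is supplied. The article's single SD and single correlation are also compatible with compound symmetry, where alpha is exactly 2.5%, and the 5.8% figure needs decay with no measurement error on a rater-scored scale.

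Much of this stands. A reader might infer that the primary test does exceed 2.5%. The document does not support that: the literal model holds its level, and the size of any excess depends on correlations that are not given. A reader might also infer that the secondary outcome, "the rate of change of MDS-UPDRS composite scores of parts I–III and of part III from baseline to 104 weeks", is affected still more. The article states no model for that outcome, so no such claim can be made.

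What does not stand is that the issue is pure silence. The article makes a positive choice about how repeated measurements and baseline enter the model. That choice does not match the endpoint it defines and powers, and a SAP that followed the wording would inherit the mismatch. Naming the patient effect twice is loose wording and would not by itself change the estimate.

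**Conclusion.** The point holds in conditional form. As written, the primary model estimates a visit-averaged arm difference with type I error about 2.5%, not the Week 104 difference conditional on baseline. If a Week 104 contrast is taken from the same random-intercept model with model-based standard errors, the SE is too small whenever correlation decays or individual slopes vary. One-sided alpha is then about 3–6% with SD 14 and correlation 0.7, up to about 8% if the SD rises over time, and 2.5% if variance and correlation are exactly constant. Neither reading gives a sound Week 104 analysis without further specification. The figures rest on assumed between-visit correlations, and the unseen SAP may already resolve the matter.

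**What to change.** For the primary analysis, state in the protocol and SAP before database lock:

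- baseline MDS-UPDRS I–III as a fixed covariate;
- visit and arm-by-visit fixed effects, alongside the minimisation factors and site effect;
- an unstructured within-participant covariance over weeks 20–104, replacing the participant random intercept and the duplicate patient effect;
- a pre-stated fallback if that model does not converge, using a simpler structure with robust standard errors;
- the arm difference at Week 104 as the primary contrast.

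The cost is wording only. Five post-baseline visits in 330 participants readily support an unstructured matrix, and no new data are needed. The interval may be somewhat wider than under compound symmetry. The sample size is unchanged, because Step 1 already uses the Week 104 variance: 132 completers per arm, SE about 1.23, power 90.15%, N = 330.

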### Data sharing

Data will be available for sharing within 6–12 months of the trial end date. Researchers wishing to access ASPro-PD data should contact the Trial Management Group in the first instance.

## Discussion

The identification of *GBA1* variants as genetic risk factors for PD has focused attention on both GCase and lysosomal function as targets for therapeutic interventions to improve the trajectory of PD.

Ambroxol has extensive preclinical and early clinical evidence to support its trial in PD [11]. Moreover, ambroxol has an established safety profile, thanks to its long-standing use as a mucolytic agent. The results from the phase 2 study in PD extend this profile by demonstrating no adverse impact on the response to dopaminergic medications in PD [21]. This finding enabled the current study design assessing ambroxol, allowing standard of care dopaminergic medications as background therapy.

Our study includes a genetically stratified PD population and is the largest ambroxol study to date. There are several challenges to the design of disease modification trials in PD and there is no uniformly accepted model [34–36]. The design of ASPro-PD has benefitted from input and advice from several experts in the field to provide an optimised approach to recruitment and end point analysis.

We chose to recruit participants both with and without *GBA1* variants, to determine whether ambroxol has a beneficial effect in both populations, as is suggested by pre-clinical studies. Even though this will not affect the primary endpoint, we aim to recruit an equal number of *GBA1*-positive and *GBA1*-negative participants. Additional statistical analysis will be carried out to determine whether ambroxol has a differential effect between the subgroups. Moreover, *GBA1* variants were categorised as “severe” and “non-severe” and this subgroup will also be used as a minimisation factor for additional analysis.

A maximum age limit of 75 years was set to optimise the potential for follow-up during the 2.5 years of observation. Duration of disease was set at a maximum of 7 years because beyond this, the rate of decline in MDS-UPDRS slows and renders it more difficult to demonstrate a change in progression [37]. Participants will be on stable symptomatic therapy for at least 3 months prior to randomisation. They will continue therapy, but increased medication, preferably in the form of levodopa, will be allowed if considered necessary by the patient or physician. This will facilitate both recruitment and reduce dropouts.

The primary outcome measure of MDS-UPDRS I–III was supported by patient participation and confirmed following regulatory advice. The inclusion of parts I and II provides patient-driven outcomes, particularly relevant for a phase III study. Part III is measured in OFF to provide less variation and provide greater sensitivity to change [38]. A 2-year treatment period was considered the minimum to enable a meaningful difference in the primary endpoint to emerge between the treatment arms. The 6-month open label treatment period was included to both improve patient recruitment to the blinded placebo-controlled phase, and to provide the drug exposure experience required by the UK regulatory authority. The option for CSF analysis will allow establishing the relationship between changes in ambroxol levels and effect size, confirmation of target engagement with GCase protein levels, and the measurement of biomarkers including alpha-synuclein and p-tau. The biomarker outcomes have been selected to measure target engagement (blood and CSF GCase activity and protein level, CSF substrate levels) and effect on markers of neurodegeneration (CSF alpha-synuclein, TAU protein, NFL).

This study provides the opportunity to determine if ambroxol can slow the progression of symptoms in PD and whether this effect is beneficial to the whole PD population or those with *GBA1* variants.

## Data Availability

Data will be available for sharing after the trial end date. Researchers wishing to access ASPro-PD data should contact the Trial Management Group in the first instance.
